## Abstract

**Background:**

Unstable angina (UA) is a critical subtype of acute coronary syndrome (ACS). Myocardial injury is a key determinant of disease progression and long-term prognosis, yet it often persists despite standard therapy. In addition, residual inflammation remains an important risk factor for adverse outcomes. Xueshuantong Injection Lyophilized (XST), derived from *Panax notoginseng* saponins (PNS), has shown potential to reduce myocardial injury and modulate inflammatory responses in cardiovascular disease, but its efficacy in UA has not been fully evaluated.

**Methods:**

This is a randomized, parallel control, double-blind, small-sample exploratory clinical trail. Participants will be recruited from Xiyuan Hospital, China Academy of Chinese Medical Sciences (Beijing, China). Eligible patients with UA will be randomized into two groups. The intervention group will receive XST 500 mg intravenously once daily for 7 days, and the control group will receive XST 25 mg intravenously once daily for 7 days. The primary outcome is CK-MB at Day 7. Secondary outcomes are cTnT, NT-proBNP, inflammatory/endothelial biomarkers (hs-CRP, IL-6, MMP-9, VEGF, HMGB1), and angina-related parameters (attack frequency, symptom severity).

**Ethics and Registration:**

The trial has been approved by the Ethics Committee of Xiyuan Hospital and registered in the ITMCTR on March 21, 2025, http://itmctr.ccebtcm.org.cn (No. ITMCTR2025000552).

**Conclusion:**

This exploratory study will evaluate the efficacy and safety of XST in reducing myocardial injury and residual risk in UA patients, providing evidence for future large-scale confirmatory trials.

## Introduction

Unstable angina (UA), a critical subtype of acute coronary syndrome (ACS), represents a major acute cardiovascular event alongside myocardial infarction (MI). Cardiovascular diseases (CVDs) collectively account for represent approximately 30% of global mortality, with ACS remaining a predominant contributor to cardiovascular-related deaths. Without timely intervention, UA carries a high risk of progression to MI, potentially leading to severe complications or mortality (1–3). In China, the burden of CVD continues to rise, with mortality rates attributable to CVD reaching 46.74% in rural and 44.26% in urban populations, exerting substancial pressure on healthcare infrastructure (4). Although contemporary revascularization strategies and pharmacotherapies [including percutaneous coronary intervention (PCI) and optimized antiplatelet regimens] have improved outcomes, patients remain at high risk for recurrent cardiovascular events. Current therapeutic paradigms prioritize antiplatelet agents and lipid-lowering strategies but lack targeted interventions to MI and residual inflammatory-metabolic risk. Despite advances in PCI and pharmacotherapy, 20%–30% of UA patients still experience perioperative myocardial injury—a subclinical entity defined by elevated high-sensitivity cardiac troponin (hs-cTn) levels—that independently predicts adverse outcomes (5). Recent evidence further demonstrates that elevated cardiac troponin I and B-type natriuretic peptide (BNP) levels independently predict major adverse cardiovascular events (MACE) and all-cause mortality in hemodialysis patients, with synergistic risk stratification when combined (6).

Xueshuantong Injection Lyophilized (XST) is a standardized traditional Chinese medicine (TCM) formulation primarily composed of *Panax notoginseng* saponins (PNS). With documented therapeutic effects in promoting blood circulation, resolving stasis, and improving vascular patency, XST is clinically used as an adjuvant therapy for ACS (7). Modern pharmacological studies have elucidated its neuroprotection mechanisms, including anti-inflammatory actions through suppression of PI3K-Akt signaling and endothelial function enhancement via improved nitric oxide bioavailability, offering multi-target modulation of ACS pathophysiology (8–11).

We previous conducted a multicenter, clinical trail (Registration No. ChiCTR1800015911) in provinces/municipalities in China from 2020 to 2022 (12). The aim of this study was to evaluate the efficacy and safety of XST in combination with dual antiplatelet therapy on MACE in patients with UA. A total of 1229 UA patients from 16 provincial administrative regions in China were enrolled in the study. The results of the median follow-up of 6 months showed that the incidence of MACE was reduced by 46.7% in the XST group compared with the control group, with time to MACE onset prolonged (27.88 vs. 19.60 days), and no significant difference in major bleeding events between the two groups. Although this trial confirmed that XST significantly reduced MACE risk, the underlying mechanisms remained unclear. Based on this, we designed the present study to test the hypothesis that XST may exert cardiovascular protection by attenuating myocardial injury and ameliorating residual inflammatory risk, as assessed by biomarkers including CK-MB, cTnT, NT-proBNP, hs-CRP, IL-6, MMP-9, VEGF, and HMGB1. This trial aims to elucidate the pleiotropic cardioprotective mechanisms of XST and provide evidence for its integration into precision secondary prevention strategies.

## Methods and analyses

### Study design

This randomized, double-blind, parallel-controlled, exploratory clinical trial (Registration NO. ITMCTR2025000552) was prospectively registered prior to patient enrollment. Participants will be recruited from Xiyuan Hospital, China Academy of Chinese Medical Sciences (Beijing, China), and all trial data will be collected from this cohort. The study is designed evaluate XST as an adjunctive therapy for patients with UA, with a primary focus on its potential to attenuate myocardial injury and reduce residual cardiovascular risk by modulating microvascular thrombosis and chronic inflammation. The findings are expected to provide evidence supporting the cardioprotective role of XST and its potential integration into precision-oriented secondary prevention strategies.

Eligible participants will be randomized into two groups: the treatment group will receive XST 500 mg, while the control group will receive XST 25 mg. Written informed consent (see online supplemental material) will be obtained from all participants or their legal representatives after eligibility screening and before randomization. A detailed flowchart of the study protocol is provided in Figure 1.

**Figure 1 F1:**
[figure not shown]
The flow chart of the trial.

## Participants

### Diagnostic criteria

The diagnosis of UA was made in accordance with the 2019 European Society of Cardiology (ESC) Guidelines for the diagnosis and management of chronic coronary syndromes (13) Diagnostic criteria included frequent anginal episodes, ST-segment depression 0.1 mV in two or more contiguous leads, and/or symmetrical T-wave inversion. Diagnostic confirmation was based on findings from echocardiography and myocardial enzyme analysis.

The diagnosis of cardiovascular blood stasis syndrome was based on the formulation principles and indications of the lyophilized XST injection, and referenced the 2018 Diagnostic Criteria for Evidence Elements of Coronary Heart Disease Angina Pectoris established by the Cardiovascular Disease Branch of the Chinese Medical Association (14). Primary symptom: stabbing chest pain with fixed location; Secondary symptoms: chest tightness, palpitations, fatigue, dark complexion; Tongue and pulse: dark purple tongue with petechiae or ecchymosis, thin coating; pulse choppy or intermittent. Diagnosis requires the primary symptom plus at least one secondary symptom, in combination with tongue and pulse findings.

### Inclusion criteria

Patients meeting all of the following conditions will be eligible for enrollment in this study:
1.Diagnosis of coronary artery disease (CAD): Fulfillment of the diagnosis of CAD diagnosis with at least one of the following criteria: (1) Definite history of myocardial infarction; (2) Previous coronary artery revascularization (PCI) (3) Coronary angiography demonstrating ≥50% luminal stenosis in at least one major coronary artery; (4) Evidence of myocardial ischemia confirmed by cardiac magnetic resonance imaging or nuclear myocardial perfusion imaging.2.Diagnosis of UA: Meeting the diagnostic criteria for UA and at least one of the following: (1) Electrocardiographic evidence of transient or persistent ST-segment deviation ≥0.1 mV in one or more leads; (2) TIMI risk score ≥3;3.Traditional Chinese medicine (TCM) diagnosis: Diagnosis of cardiac blood stasis syndrome according to TCM criteria.4.Age; 45–75 years old.5.Informed consent: Hospitalized patients who voluntarily agree to participate, accept study medication, and sign a written informed consent form. The informed consent process will be conducted in accordance with the relevant provisions of Good Clinical Practice (GCP).

### Exclusion criteria

Patients meeting any of the following conditions will be excluded from this study:
1.Severe cardiovascular conditions: (1) New York Heart Association (NYHA) class IV heart failure; (2) UA with high short-term risk stratification; (3) Uncontrolled grade III hypertension (systolic blood pressure ≥180 mm Hg and/or diastolic blood pressure ≥110 mm Hg).2.Increased risk of bleeding: History of major organ bleeding within the past six months; Thrombocytopenia or coagulation abnormalities; Active bleeding within the past month.3.Severe comorbidities or contraindications: Abnormal liver or renal function tests; Pregnant or breastfeeding women, or those planning pregnancy during the study period; Patients with malignant tumors, severe psychiatric disorders, or other serious systemic diseases affecting survival.4.Patients who refused to participate in this study.

### Randomization and blinding

This study used a central stratified block randomization method. We used statistical software to create two treatment groups (test and control) for 100 patients. Each patient from number 01 to 100 was randomly assigned to a group using a treatment allocation table. The blinding process was done by statisticians.

This was a double-blind study. The control group received a very low dose, and both groups had the same number of patients (1:1 ratio). The study drugs and control were made to look identical in packaging and appearance. The packaging followed the random allocation table and blinding rules. The sealed blinding codes were stored in two copies at the clinical trial institution.

### Interventions

All enrolled patients will receive guideline-recommended standard Western medical therapy, including dual antiplatelet therapy, statins, β-blockers, and ACEI/ARB, as appropriate. On this basis, patients will be randomly assigned to receive:
1.Treatment group: The patients will be treated via an intravenous drip with 500 mg XST diluted with 250–500 mL of 5% glucose injection or sodium chloride injection, once per day for 7days;2.Control group: The patients will be treated via an intravenous drip with 25 mg XST diluted with 250–500 mL of 5% glucose injection or sodium chloride injection, once per day for 7days.The choice of a low-dose control (25 mg/day) was made solely to preserve the integrity of blinding, as this minimal dose is expected to have negligible pharmacological effect and approximate placebo. This design ensured that both groups received visually identical interventions, minimizing the risk of unblinding among patients and nursing staff.

### Outcome measurements

Primary and secondary efficacy outcomes were measured once pre-treatment and once post-treatment for a total of two times.

### Primary outcomes

The primary efficacy endpoint of this study is the change from baseline in CK-MB at Day 7.

### Secondary outcomes

1.Change from baseline in cTnT and NT-proBNP at Day 7.2.Inflammatory and endothelial biomarkers: changes from baseline to Day 7 in hs-CRP, IL-6, MMP-9, VEGF and HMGB1.3.Angina-specific parameters: changes in attack frequency, symptom severity.

### Safety assessment

An adverse event (AE) refers to any unintended medical occurrence observed during the trial, regardless of its relationship to the study intervention. Throughout the study period, researchers will monitor vital signs (e.g., blood pressure, heart rate); Perform blood tests, urinalysis, and assess renal/liver function (at baseline and post-treatment). Document any clinically significant abnormalities or AEs identified during the trial.

If an AE occurs, the research team will clinically evaluate whether to pause participant involvement, initiate diagnostic procedures, or adjust treatment plans. For severe AEs (SAEs), immediate medical intervention will be prioritized to ensure participant safety. All SAEs must be reported to the institutional ethics committee within 24 h of identification.

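### The 24-hour reporting rule is tied to severe rather than serious adverse events; probably a wording slip, but it sits in an operative safety rule and nothing else in the document corrects it

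*Protocol article*

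**What the plan says.** Everything relevant is in the Safety assessment section of the protocol article.

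- It defines an adverse event broadly: "An adverse event (AE) refers to any unintended medical occurrence observed during the trial, regardless of its relationship to the study intervention".
- For adverse events in general it asks for recording: "Document any clinically significant abnormalities or AEs identified during the trial". It also has the research team judge clinically whether participation, diagnostics or treatment need to change. Neither instruction carries a deadline or sends a report outside the team.
- It then introduces the abbreviation: "For severe AEs (SAEs), immediate medical intervention will be prioritized to ensure participant safety".
- The sentence after that sets the expedited duty: "All SAEs must be reported to the institutional ethics committee within 24 h of identification".

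The Inclusion criteria add one relevant fact, that participants are already inpatients at entry: "Hospitalized patients who voluntarily agree to participate, accept study medication, and sign a written informed consent form".

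**The concern.** Severity and seriousness are different attributes of an adverse event. Severity grades intensity. Seriousness classifies consequence: death, threat to life, new or prolonged hospitalisation, lasting disability, or a comparably important medical event. Expedited reporting conventionally rests on seriousness, because the body overseeing the trial needs to hear quickly about harm that matters, however intense it felt or looked at the time.

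The article prints the intensity word and hangs a mandatory duty on the abbreviation so defined. If site staff follow the text as it stands, the trigger for notifying the ethics committee is the wrong attribute. The inpatient setting makes the distinction practical. An event of moderate intensity that lengthens the current stay is serious by the usual outcome criteria, but nothing in the word severe would prompt anyone to report it.

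**Working it through.** No arithmetic applies. The check is whether the text, read as a rule, sends the right events down the 24-hour route, and whether any other part of the document repairs it.

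**Step 1. What does SAE mean here?** The abbreviation is expanded once, in the Safety assessment section, as severe AEs. No other section expands it.

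**Step 2. Is seriousness defined or used elsewhere?** The word serious appears once, in the Exclusion criteria, where it describes systemic diseases that affect survival. It is never applied to adverse events. The Statistical analysis section refers only to safety outcomes in general and does not mention SAEs.

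**Step 3. What does the 24-hour rule cover?** It covers all SAEs. Substituting the only expansion available, it covers all severe adverse events.

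**Step 4. Sort events by the two attributes and apply the literal rule.**

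| Event | Rule as printed | Rule tied to seriousness |
|---|---|---|
| Severe and serious | Ethics committee within 24 h | Ethics committee within 24 h |
| Severe, not serious | Ethics committee within 24 h | Recorded and evaluated, no 24 h duty |
| Not severe, serious | Recorded and evaluated, no 24 h duty | Ethics committee within 24 h |
| Neither | Recorded and evaluated, no 24 h duty | Recorded and evaluated, no 24 h duty |

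The two rules agree in the first and last rows and differ in the middle two. The second row costs an unnecessary report. The third row is the one that matters: such an event stays within the research team with no stated deadline.

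**Step 5. How many events fall in the third row?** The document gives no adverse event rates, no expected events and no severity scale, so this cannot be estimated.

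**The case against.** The strongest reply is that one word is wrong and little follows from it. Four parts of that reply deserve an answer.

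- **It is a slip.** The abbreviation SAE and a 24-hour clock normally belong to seriousness, and the article has other slips of language. The Abstract calls the study a clinical trail, and the Sample size section gives α as 0.05% where the Statistical analysis section gives 0.05. This stands. A reader might infer that the trial deliberately chose intensity as its reporting trigger, but the document does not support that.
- **The full protocol may have it right.** An article commonly leaves the list of seriousness criteria, the severity grades and the form fields to the full document, so their absence here is not a fault. This stands too. It does not remove the point, which concerns a term that is printed wrongly and then used in a mandatory rule.
- **Severe is not tied to a grade here.** With no mild, moderate and severe scale in the text, one cannot say for certain how a given event would be classed. This limits any claim about particular events. It does not make the word mean serious.
- **Events are still captured.** Every adverse event is to be recorded, whatever its cause, and evaluated clinically, and the safety set includes everyone dosed. This stands: what is at risk is prompt notification, not the record itself.

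Two further inferences also fail. A reader might suppose that the SAE rates of the two arms would be distorted. No SAE count or table by arm is described, and observing that one event is a large share of a small arm says nothing about this wording. A reader might also suppose that results could not be set beside the earlier multicentre XST trial. The Introduction gives no SAE definition or rate for that trial, so the comparison cannot be judged.

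**Conclusion.** The point holds as a minor correction. As printed, the 24-hour duty to notify the ethics committee depends on intensity, and an event that is serious in outcome but not severe has no stated reporting deadline. This rests on two things: reading the rule literally, and the ordinary distinction between severity and seriousness. If the full protocol and the site procedure already define SAE by outcome, the practical effect is nil and only the article needs correcting. If they repeat the article's wording, a safety duty runs on the wrong attribute.

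The size cannot be expressed as a number from this document. The sample size, the primary and secondary efficacy analyses and the definitions of the analysis sets are untouched. The document does not support a stronger claim that reportable events will be missed or that safety results will be biased between arms.

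**What to change.** 1. In the Safety assessment section, replace severe AEs (SAEs) with serious adverse events (SAEs).
2. Tie the 24-hour rule to seriousness as defined by outcome in the full protocol, and refer to that definition.
3. Confirm that the full protocol and the reporting procedure used at the site carry the same definition.

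The sentence that contains the expansion also governs the medical response to such events. The sponsor should therefore check that its scope is still as intended once the term changes. That is a clinical matter, and no view on it is offered here.

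The cost is a small edit and one check against the full protocol, with possibly a few more expedited reports. No new data field, analysis or table is needed for this point.

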### Data collection and management

In this experiment, an electronic data acquisition system was used to create an electronic case report form, and the data were collected and managed online through the Internet. After the blind review of the data is completed and locked, the blind is uncovered for the first time when the statistician conducts statistical analysis, and the corresponding processing group (i.e., group A and Group B) is opened. After the statistical analysis, the study report (discussion draft) was written by the main researcher, and the blind was uncovered for a second time, and the corresponding study group of the treatment group was selected.

### Sample size

The sample size was determined based on the sole primary endpoint (CK-MB). Based on previous reports of CK-MB changes in unstable angina patients (15), we conservatively assumed a standardized effect size of d = 0.50 (medium effect). With two-sided α = 0.05% and 80% power, the required sample size for a two-sample t-test was 63 per group. Because the primary analysis will use ANCOVA with baseline adjustment, the sample size was reduced by a factor of (1–R²), assuming R² = 0.40, yielding approximately 38 per group. After considering a 20% attrition rate, the final target enrollment was 50 per group, 100 in total. Calculations were performed using G*Power v3.1.9.7

### Analysis sets

#### Full analysis set (FAS)

Defined according to the intention-to-treat principle, including all randomized participants who received at least one dose of study medication and had at least one post-baseline efficacy assessment. The FAS will be used for the primary efficacy analysis.

#### Per-protocol set (PPS)

Includes participants who completed the study without major protocol deviations (e.g., non-adherence, prohibited concomitant medication, significant missing data). The PPS will be used for sensitivity analyses to evaluate the robustness of the results.

#### Safety set (SS)

Includes all participants who received at least one dose of study medication. The SS will be used for safety analyses.

### Statistical analysis

Statistical analyses will be performed using R software (version 4.3.2). All tests will be two-sided with α=0.05. The primary outcome (Day-7 CK-MB, baseline-adjusted) will be analyzed by ANCOVA, with treatment group as a fixed factor and baseline CK-MB as a covariate. Major concomitant medications will also be included as covariates, specifically: (1) dual antiplatelet therapy; (2) statins; (3) β-blockers; and (4) ACEI/ARB. For each class, exposure during the 7-day intervention window will be coded “Yes” if the drug was taken on ≥80% of on-study days (≥6/7 days), otherwise “No”. The treatment effect will be reported as the adjusted mean difference with 95% CI. Secondary outcomes will be analyzed using ANCOVA or appropriate parametric/non-parametric tests with the same covariates. *P*-values for these outcomes will be nominal without multiplicity adjustment and interpreted as exploratory. Safety outcomes will be summarized descriptively by incidence (*n*, %) and compared between groups using χ² or Fisher's exact test, as appropriate.

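### The primary ANCOVA adjusts for concomitant-drug use recorded after randomisation, which would bias the CK-MB treatment effect if study treatment alters that use

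*Protocol article*

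**What the plan says.** All references are to the protocol article.

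- **Statistical analysis, model.** Day-7 CK-MB "will be analyzed by ANCOVA, with treatment group as a fixed factor and baseline CK-MB as a covariate". The next sentence extends the model: "Major concomitant medications will also be included as covariates", naming four drug classes.
- **Statistical analysis, timing and coding.** Each indicator is set by use over the treatment week: "exposure during the 7-day intervention window will be coded" at one of two levels. The level Yes applies "if the drug was taken on ≥80% of on-study days (≥6/7 days), otherwise" the level is No. Secondary outcomes use the same covariates.
- **Interventions.** Study drug is infused daily for 7 days, which is the window over which the covariates are recorded. Background therapy is described as "including dual antiplatelet therapy, statins, β-blockers, and ACEI/ARB, as appropriate", so it can differ between patients and over time.
- **Safety assessment.** After an adverse event the team will "clinically evaluate whether to pause participant involvement, initiate diagnostic procedures, or adjust treatment plans".
- **Per-protocol set.** This is the only sensitivity analysis named. It changes the population, not the covariates.
- **Sample size.** The ANCOVA saving (R² = 0.40) is credited to baseline adjustment. The drug terms are not mentioned.

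**The concern.** Covariates in the primary model of a randomised trial should be fixed before treatment starts. Baseline CK-MB is. The four drug indicators are not: they record what happened during the treatment week. A variable that treatment can influence may lie on the path from treatment to outcome, in which case adjusting for it removes part of the effect. It may also share unmeasured causes with the outcome, in which case adjusting for it creates a difference between arms that assignment did not produce.

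The article leaves routes open for such an influence. Background therapy may vary with the patient's course, plans may be adjusted after an adverse event, and angina frequency and severity are themselves outcomes that the study drug is hoped to improve. What is at stake is the meaning of the adjusted mean difference for the sole primary endpoint, and of the secondary estimates that use the same covariates.

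**Working it through.** **1. The plan's own sample size, to see whether it depends on the drug terms.** Inputs from Sample size: d = 0.50, power 80%, R² = 0.40, attrition 20%; two-sided α = 0.05 from Statistical analysis.

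- n per group = 2(1.960 + 0.842)² / 0.50² = 62.8, so 63 (stated: 63; the exact t calculation gives 64).
- 63 × (1 − 0.40) = 37.8, so 38 (stated: about 38).
- 38 / (1 − 0.20) = 47.5, so 48 (stated: 50, a small rounding up).

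The figures reproduce with baseline adjustment alone. With residual variance 0.60, power is 80.3% at 38 per group and 82.3% at the 40 completers that 50 × 0.80 leaves. Dropping the drug terms changes none of this.

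**2. When adjustment biases the estimate.** For one indicator M (1 = coded No):

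adjusted effect = total effect − γ × (difference between arms in the proportion with M = 1),

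where γ is the pooled within-arm slope of CK-MB on M. If the arms do not differ in exposure, the second term is zero. In simulation (100 patients, 3,000 trials per setting) with exposure related to severity but not to treatment, a true effect of −0.50 SD was estimated as −0.50 with and without the drug term.

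**3. Treatment-driven link: loss of effect.** Assumptions, not from the article: true effect −0.50 SD, residual variance 0.60, one indicator generated from the treated outcome itself with latent correlation ρ, and 10 to 30% of controls coded No. Worked case, ρ = 0.6 and 10% No in controls:

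- The treated arm's latent mean shifts by 0.6 × (−0.50/√0.60) = −0.387, so its No rate falls to 4.8%, a difference of −0.052.
- γ = 0.943.
- Adjusted effect = −0.50 − 0.943 × (−0.052) = −0.451.

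| ρ | No in controls | No in treated | γ | Adjusted effect | Loss |
|---|---|---|---|---|---|
| 0.2 | 10% | 7.9% | 0.307 | −0.494 | 1% |
| 0.2 | 30% | 25.7% | 0.259 | −0.489 | 2% |
| 0.3 | 10% | 7.0% | 0.464 | −0.486 | 3% |
| 0.3 | 30% | 23.6% | 0.390 | −0.475 | 5% |
| 0.6 | 10% | 4.8% | 0.943 | −0.451 | 10% |
| 0.6 | 20% | 11.0% | 0.843 | −0.424 | 15% |
| 0.6 | 30% | 18.1% | 0.793 | −0.406 | 19% |

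**4. Opposite direction.** Assumptions, not from the article: 80% of controls coded Yes, an unmeasured severity factor drives both exposure and CK-MB, and treatment lowers the Yes rate.

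- Yes falls to about 60%: a true effect of zero is estimated as −0.07 to −0.12 SD, with type I error 7.6 to 13.5%; a true −0.50 becomes −0.58 to −0.62.
- Yes falls to about 44%: a true zero is estimated as −0.13 to −0.22 SD, with type I error 11 to 27%.

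The model with baseline alone stayed within 0.005 SD of the truth in every setting, with type I error 4.3 to 5.1%.

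**5. Price of dropping the terms.** Where exposure is prognostic but unaffected by treatment, power at 50 per group was 89.6% without the term against 90.5% with it, and 88.3% against 90.7% when severity mattered more.

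**6. The coding rule.** For seven on-study days, 0.80 × 7 = 5.6, so six days are needed and both forms agree. For shorter stays they part: 4 of 4 days is 100%, hence Yes by the percentage, but 4 is fewer than 6, hence No by the count. With five or fewer on-study days, Yes can never be reached by the count.

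**The case against.** The strongest case on the other side is that the risk is conditional and probably modest. Double-blinding with identical packaging limits prescribing that follows knowledge of the arm. Patients at increased bleeding risk or with high short-term risk are excluded, and the earlier XST trial is reported as showing no significant difference in major bleeding. A patient on daily treatment must miss at least two of seven days to be coded No. Patients never prescribed a class are also coded No, which mostly reflects prescribing and not a response to study drug. The 10 to 19% loss needs the study drug roughly to halve No coding. Even then the shift of 0.05 to 0.09 SD is about 0.3 to 0.5 standard errors at 40 per group (√(0.60 × 2/40) = 0.17). The type I error figures need a fall in exposure that nothing in the article suggests. The trial is small and exploratory.

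All of this stands as a limit on size. It does not change the timing of the covariates, and blinding does not prevent changes driven by adverse events or clinical response.

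Three stronger readings are tempting and are not supported:

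- That the adjustment in itself invalidates the randomised comparison. Bias requires treatment to change exposure; a link with the patient's clinical course alone produces none.
- That the covariates are almost constant because every patient receives these drugs. The sentence in Interventions ends with a qualifier that lets therapy vary by patient, so near-constancy is possible but not established.
- That the coding conflict reaches the 20% expected attrition. Efficacy is measured once after treatment, and a patient without a Day-7 CK-MB contributes no observed outcome to the primary comparison. The conflict matters only for those who stop early and still have that value.

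**Conclusion.** The point holds as a conditional one and should be fixed. The article itself fixes post-randomisation drug exposure as covariates in the primary and secondary models, and no named analysis would reveal a resulting distortion. Whether bias occurs, and its sign, depends on whether study treatment alters exposure; the article gives no figure for this. The range in the illustrations (none, 1 to 5%, 10 to 19% loss, or exaggeration under other mechanisms) rests on the assumptions set out above and uses one indicator instead of four. It shows what could happen and is not an estimate for this trial. The timing of the covariates is certain; the harm is not. The coding contradiction is real but narrow.

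**What to change.** Before unblinding, redefine the primary model as treatment group, baseline CK-MB and the stratification factors used at randomisation (the article states stratified blocks but does not name the factors). Remove the on-treatment exposure terms from the primary and secondary models. If adjustment for medication is wanted, replace them with status for each class recorded before the first dose. Report 7-day exposure by arm in a descriptive table or a clearly labelled supplementary analysis, under one coding rule: either a percentage of on-study days, with the denominator defined, or a fixed count of days.

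The cost is a wording change. No added patients are needed, and the sample size stands because R² = 0.40 is attributed to baseline adjustment. The downside is a possible small loss of precision if on-treatment exposure is prognostic (about 1 to 2 points of power in the illustration); pre-dose status may recover part of it.
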